#### Blinding

This is an open-label, clinical trial; therefore, the procedures will not be blinded because participants will need to visit their physician to approve their randomized medication. Pharmacists, primary care providers and research personnel will know which medication participants have been assigned to.

### Medication

Compliance with the prescribed regimen will be measured by participants’ self-report follow-up assessments at weeks 4, 8, and 12. In addition, saliva sample kits will be mailed out to participants at week 4 for the biochemical analysis of drug levels to confirm medication compliance. Participants will be compensated for each sample received.

#### Behavioral Support

All eligible participants will receive 12 weekly motivational emails for the duration of treatment. The emails include tips on several things, other than the medications, which participants can do to help them quit smoking. The contents of the emails vary from week to week (Multimedia Appendix 1).

#### Participant Follow-Up by Email

Participants will be contacted by email at weeks 4, 8, 12, 26, and 52 to complete follow-up surveys. The follow-up surveys will collect data on changes to the participants’ smoking pattern and medication use and any possible adverse reactions experienced. During each follow-up survey, participants will be asked whether they have experienced any adverse events. If the participants at any point are experiencing intolerable adverse events, they can contact the study personnel to withdraw from the study. They will be compensated for all the saliva and genetic samples that they had submitted prior to being withdrawn. There will be no modifications to interventions even if adverse side effects are reported. Instead, participants will either be discontinuing their treatment or will be advised to speak with their physician regarding the intervention. If participants withdraw from the study, they will still be asked to complete follow-up surveys.

#### Cost-Effectiveness

To make an impact on the prevalence of smoking in the overall population, it is necessary for an intervention to reach a high number of people. Efficacious pharmacotherapies are available for smoking cessation but their reach is typically limited. To the best of our knowledge, this is the first study to attempt the mass distribution of prescription medications for smoking cessation using a randomized study design. The method proposed has been previously demonstrated by the investigators of this study to be logistically feasible and effective in terms of cessation rates [18] and has provided crucial evidence for an approach that has the potential to make a significant impact on cessation rates at a population level by demonstrating a way to take full advantage of the available smoking cessation aids.

All recruitment, consenting, and data collection are Web-based. The mail-order pharmacy is less expensive than dispensing through a research pharmacy, and we do not need to pay physicians to recruit their patients into studies because subjects self-identify first and then go to their physician (in Canada, all physician visits are paid for by our universal health care system). As such, this large randomized trial can be extremely cost effective with an estimated cost of under Can $150,000. We aim to provide medication to 1000 participants; therefore, the cost per enrollment is estimated to be Can $133.33. The 52-week CAR in the varenicline-treated group is assumed to be 18% compared with 12.5% in the bupropion group. Therefore, the cost per quit is estimated to be about Can $873.36 plus Can $33.70 for a visit to the prescriber if the government’s universal health plan is billed; this is much lower compared with the economic burden of continued smoking. A report published in 2015 estimated the annual health care cost in Canada to be Can $3071 per smoker [20].

### Primary Outcome

The primary outcome measures will be related to the effectiveness of treatment. The primary outcome will biochemically confirm 30-day continuous abstinence by mailed-in salivary COT 26 weeks after the start of treatment. Secondary outcome variables will be self-reported 30-day continuous abstinence at the end of the treatment (weeks 9-12) and at weeks 26 and 52; this is defined as not having smoked, even a puff, in the past 30 days and lack of relapse during this period. Other outcome variables include self-reported 7-day PPA measured at weeks 4, 8, 12, 26, and 52. The 7-day PPA is defined as not having smoked, even a puff, over the last 7 days.

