Therefore, although there is limited evidence for the superior long-term efficacy of varenicline, no study has assessed the real-world effectiveness of these medications for long-term abstinence. This is important because of some significant differences between clinical trials and real-world settings, which could influence cessation treatment outcomes; for example, clinical trials have strict eligibility criteria, excluding participants with certain comorbidities. Therefore, participants in these studies are in better health compared with the general population. In addition, treatment with medications in clinical trials is accompanied by one-on-one smoking cessation behavioral counseling often on a weekly basis, which is largely unavailable in real-world settings [7]. These factors together have the potential to restrict the external validity of clinical trial findings. As such, there is a need to assess the real-world effectiveness of these prescription medications at a population level to further strengthen the evidence base for the effective treatment of tobacco dependence.

Even though proven efficacious in clinical trials, according to the Canadian Tobacco Use Monitoring Survey in 2007, less than half of smokers who have ever attempted to quit have used a smoking cessation aid [9]. Most of these smokers identify the lack of access to adequate and evidence-based information, in addition to the cost, as reasons for not using these smoking cessation pharmacotherapies [9]. Furthermore, bupropion and varenicline are only available by a prescription from a licensed practitioner. Therefore, in addition to knowledge and affordability, their population-level impact is limited by accessibility. Furthermore, smoking cessation clinics are limited in number, and a survey conducted in Canada demonstrated that the occurrence of smoking cessation discussion between physicians and patients is not common. In fact, of 88% of smokers who visited a primary care physician in the year prior, only half received any advice on quitting or reducing smoking [10]. Efforts to address these barriers could greatly improve the use and effectiveness of these smoking cessation medications in real-world settings [11]. Furthermore, mass distribution approaches, bypassing clinics and physicians, have been successful for nicotine replacement therapy [12,13]. However, bupropion and varenicline have the potential to make a greater impact, given their superior results from clinical trials.

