**Figure 2 figure2:**
[figure not shown]
Participants’ flowchart. BFAS: Big Five Aspect Scale.

After submitting the completed questionnaires, individuals will be notified, through an on-screen message, whether they are eligible for the study. Those who are eligible will receive an email, including their medication assignment, the study information and consent form, a standardized letter to the doctor to convey information about the study, and a standard script for the study medication they have been assigned to for their physician (or other licensed prescriber) to sign. Because there are no in-person study visits, Salivette kits will be mailed out at the time of study enrollment to verify the participants’ smoking status.

In addition, baseline saliva sample will be used to measure the nicotine metabolite ratio, which is the ratio of 3'-hydroxycotinine and cotinine (COT) concentration; this is a validated phenotypic biomarker of the CYP2A6 enzyme activity [17]. Furthermore, Salivette kits will be sent at weeks 4, 26, and 52 to measure the salivary COT level for the biochemical verification of abstinence. Those who consent to the genetics substudy will receive a second email with the genetics study information and consent form and the Oragene saliva DNA kits by mail to collect a DNA sample for the pharmacogenetics component of the study. Participants will be compensated for each DNA (if applicable) and subsequent saliva samples received.

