### Participants

#### Inclusion and Exclusion Criteria

The following inclusion criteria will need to be met before any individual is randomly assigned to one of the 2 treatment arms: Ontario resident; having a valid email address; aged at least 19 years; current daily smoker; smoking at least 10 cigarettes per day; smoked daily for at least the past year; and have an intention to quit smoking within 30 days of receiving the medication. The following are criteria that will exclude an individual from being randomly assigned to one of the 2 treatment arms: a history of psychotic disorder (schizophrenia or bipolar disorder) or eating disorder; brain injury; seizure disorder; pregnancy, lactation, or at risk of becoming pregnant; allergy or sensitivity to bupropion or varenicline; or currently taking varenicline or Champix, bupropion or Zyban or Wellbutrin, monoamine oxidase inhibitors, thioridazine, antidepressants, or other medications containing bupropion hydrochloride.

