#### Recruitment and Randomization

The primary method of recruitment for this study will be by word-of-mouth through family, friends, or health care providers. The Smoking Treatment for Ontario Patients Study [12,13], also conducted by the investigators of this trial, has successfully built a collaborative network of providers from public health units, community health centers, family health teams, and community pharmacies across Ontario. This network of providers has proven to be effective in disseminating new treatment opportunities to smokers in their area. Interested individuals will self-identify and will be directed to enroll through the study website. Moreover, as part of the consenting procedure for those who participated in the Smoking Treatment for Ontario Patients Program, individuals will be asked whether they would like to be contacted about new research opportunities by CAMH. Those who choose “yes” will then be included in a database forming a smokers’ registry that can be contacted in case new research opportunities come up. This smokers’ registry will be another method of recruitment used for this study. Furthermore, the public will be informed about the study through CAMH social media accounts, Smokers’ Helpline, and Facebook advertisements.

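### The primary outcome confirms not smoking by salivary cotinine alone, yet nicotine replacement is neither excluded nor restricted, so smoke-free nicotine users could not be confirmed abstinent

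*Protocol article*

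**What the plan says.** All references are to the protocol article.

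- **Primary Outcome** fixes the endpoint: "The primary outcome will biochemically confirm 30-day continuous abstinence by mailed-in salivary COT 26 weeks after the start of treatment". The next sentence, on the self-reported version of 30-day continuous abstinence, gives the meaning: "this is defined as not having smoked, even a puff, in the past 30 days and lack of relapse during this period". It speaks of smoking and does not mention nicotine.
- **Setting**, in the text after Figure 2, names the verifying test: "Salivette kits will be sent at weeks 4, 26, and 52 to measure the salivary COT level for the biochemical verification of abstinence". No other marker is named. The same section says the "baseline saliva sample will be used to measure the nicotine metabolite ratio" and builds that ratio from cotinine and its hydroxylated form, so the article itself treats cotinine as a product of nicotine.
- **Inclusion and Exclusion Criteria** ends its list of exclusions with people who are pregnant or allergic, "or currently taking varenicline or Champix, bupropion or Zyban or Wellbutrin, monoamine oxidase inhibitors, thioridazine, antidepressants, or other medications containing bupropion hydrochloride". Nicotine replacement is not on the list.
- **Medication**, **Behavioral Support** and **Participant Follow-Up by Email** place no limit on nicotine products after randomization. The last of these does say: "The follow-up surveys will collect data on changes to the participants’ smoking pattern and medication use and any possible adverse reactions experienced".
- **Data Analysis** counts as smokers those who are lost to follow-up or return no saliva. It does not mention a returned, cotinine-positive sample from someone who reports not smoking.

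**The concern.** The construct and the test differ. The construct is freedom from smoking; the test responds to nicotine from any source. They coincide only if abstainers use no nicotine product at the time of sampling, and nothing in the article ensures that.

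Use is plausible in this setting. The Background lists nicotine replacement among the proven aids. It also cites, for mass distribution of nicotine replacement, the same two references that Recruitment and Randomization gives for the investigators' earlier programme. On that programme's registry the latter section says: "This smokers’ registry will be another method of recruitment used for this study". The trial is open-label and has no study visits, and participants who withdraw are still surveyed. Someone who gives up the assigned drug and quits with a nicotine product can therefore remain in the denominator.

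If such people are not confirmed, equal use in both arms lowers both quit rates and shrinks the difference. Unequal use moves the difference up or down for reasons unrelated to smoking.

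**Working it through.** **Inputs.** From Sample Size: 20% (varenicline) vs 15% (bupropion) at 26 weeks, 500 per arm, significance level .05, stated power 80%. Sidedness is not stated, so two-sided is used. The share *f* of true abstainers who are cotinine-positive only because of a nicotine product is not in the article. It is assumed, with a range of 0% to 20%.

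**Method.** Confirmed rate = true rate × (1 − *f*). The comparison is simplified to a two-proportion test at week 26 with *n* = 500 per arm:

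power = Φ{ [ |p₁ − p₂|√n − 1.96√(2p̄(1 − p̄)) ] / √(p₁(1 − p₁) + p₂(1 − p₂)) }

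**Step 1: the plan's own figure.** For 0.20 vs 0.15: 0.05 × √500 = 1.118; 1.96 × √(2 × 0.175 × 0.825) = 1.053; denominator √(0.160 + 0.1275) = 0.536. Then (1.118 − 1.053)/0.536 = 0.121 and Φ = 54.8%. A one-sided test gives 66.9%. The stated 80% is not reproduced. That is a separate matter; here 54.8% serves only as the starting point.

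**Step 2: equal use in both arms.**

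- *f* = 10%: 0.20 × 0.9 = 18.0% and 0.15 × 0.9 = 13.5%, a difference of 4.5 points. (1.006 − 1.010)/0.514 = −0.007; power 49.7%.
- *f* = 20%: 0.20 × 0.8 = 16.0% and 0.15 × 0.8 = 12.0%, a difference of 4.0 points. (0.894 − 0.962)/0.490 = −0.137; power 44.5%.

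In numbers of people, 20% and 15% of 500 are 100 and 75 abstainers. *f* = 10% removes 10 and 7.5 of them; *f* = 20% removes 20 and 15.

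**Step 3: unequal use.**

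- 20% varenicline, 10% bupropion: 16.0% vs 13.5%, a difference of 2.5 points, power about 20%.
- 10% varenicline, 20% bupropion: 18.0% vs 12.0%, a difference of 6.0 points, wider than the true 5.
- No true difference (17.5% in each arm), use 10% vs 20%: 15.75% vs 14.0%, a false gap of 1.75 points. Its standard error is √[(0.1575 × 0.8425 + 0.14 × 0.86)/500] = 0.0225, so the ratio is 0.78. The two-sided rejection rate is Φ(0.78 − 1.96) + Φ(−0.78 − 1.96), about 12% instead of 5%.

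**The case against.** A reader might infer that the plan definitely scores smoke-free nicotine users as treatment failures. The article does not say so. It gives no cotinine cut-off, and its only explicit scoring rule concerns missing responses and missing saliva. A rule for positive samples with concurrent nicotine use is something an article may leave to the full protocol or analysis plan, neither of which is shown. This stands, and the scoring must be called an inference. It does not remove the point, because the article does fix the construct and the single test, and that test cannot confirm a smoke-free nicotine user.

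A reader might also infer that nicotine use was common among abstainers here. The shared references and the registry show only that nicotine replacement was familiar in this setting. The registry is a supplementary source, with word-of-mouth named as the primary one. The 10% and 20% figures have no basis in the document, and the larger distortions in Step 3 need a twofold imbalance between arms whose direction is unknown. All of this stands.

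The article already holds a partial check. Self-reported 30-day abstinence at week 26 is a secondary outcome and does not depend on cotinine. It is not a substitute, because it also counts self-reported quitters who returned no saliva, so a gap between the two outcomes would mix both causes.

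Whether lower absolute rates would spoil the planned comparison with earlier trials depends on how those trials verified abstinence, which the article does not say. That consequence is not claimed.

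Finally, letting self-report lead for anyone who reports nicotine use weakens verification in an open-label trial without visits. This is a fair objection to replacing the strict rule, and the reason for running the comparison both ways.

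**Conclusion.** The concern holds in a limited form. The primary outcome verifies not smoking with a marker of nicotine in a population free to use nicotine products, and by inference a smoke-free user would count as not abstinent. With equal use by 10% to 20% of abstainers, the assumed 5-point difference shrinks to between 4.5 and 4.0 points, and two-sided power falls by about 5 to 10 percentage points from 54.8%. With unequal use the bias can go either way.

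These sizes rest on the assumed use rates, on the plan's 20% vs 15%, and on the inference about scoring. The documents do not support a claim that the comparison is biased in a known direction or by a known amount. The problem is worth correcting because it concerns the primary endpoint and its possible effect can be shown cheaply.

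**What to change.** 1. At weeks 26 and 52, identify nicotine-product use around the time of sampling. Use the medication-use answers already collected in the follow-up surveys, or one added item where still possible. The article reports enrollment complete and only a few one-year follow-ups outstanding, so for week 26 this will mostly mean the existing answers.
2. Report, per arm, the number of self-reported non-smokers who are cotinine-positive with such use.
3. Fix in advance, identically for both arms, a primary comparison run both ways: (a) these participants counted as smokers; (b) these participants classified by self-report. Since the article says analysis is under way, state when this was fixed relative to any comparison of the arms.
4. Base the conclusion on whether the two runs agree, and report both if they do not.

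The cost is one classification rule, one extra run and, at most, one survey item. The downside is that in run (b) confirmation rests on self-report for these participants. Run (a) gives the strict count for each arm and so shows how much depends on it. If the existing medication-use answers do not separate nicotine products, that limit should be reported.

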### Exploratory Measures and Potential Covariates

The tertiary outcome measures will be related to variations in genetic polymorphisms, metabolic factors, and personality traits observed in each treatment group. A 3-way analysis looking at the interaction between genetic polymorphism and treatment outcome, personality traits and treatment outcome, and genetic polymorphism and personality traits will be conducted; this part of the study should be considered exploratory. We have no specific hypotheses currently.

### Data Access

Datasets will only be available to CAMH research personnel only or those involved in the study. The funder does not have access to the trial dataset. Currently, there is no ability for the study data to be openly accessed by other researchers because of the restrictions placed by our REB.

### Data Analysis

Analysis of study results will be conducted using the intention-to-treat analysis, wherein all participants who are randomized to a treatment arm and receive their assigned medication are included in the final analysis whether they complete the study or respond to follow-up surveys at study end points. This method will be used to avoid any bias that can potentially arise because of crossover and dropouts, affecting the initial random assignment to treatment groups. Participants who are lost to follow-up or do not provide a saliva sample for the COT confirmation of abstinence will be considered as smokers according to recommendations by the Society for Research on Nicotine and Tobacco’s subcommittee on Biochemical Verification (2002) [21].

The baseline characteristics will be analyzed and compared between intervention groups using the Student’s *t* test for continuous variables and cross-tabs chi-square analysis for all categorical variables. Any characteristics that differ significantly across our 2 study groups will be included as covariates in all subsequent analyses. The effect of intervention over time will be evaluated using the longitudinal logistic regression analysis with abstinence as the dependent variable and treatment condition along with other baseline characteristics as independent predictors. We will construct a longitudinal generalized estimating equations (GEE) model for each binary outcome. GEE is a suitable analysis method because it accommodates for the statistical dependence among repeated observations within subjects. Because our primary outcome is abstinence from smoking (Yes or No) at each follow-up time point, GEE is appropriate because it allows for the estimation of population-averaged effects while accounting for the dependencies among the repeated measures. The data analysis for this study will be overseen by the principal investigator in consultation with the Biostatistical Consulting Service at CAMH.

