**Methods:**

This is a two-group, parallel block, randomized (1:1) open-label clinical trial. This study will be conducted online with the baseline enrollment through the study’s website and follow-up by emails. In addition, medication prescriptions will be filled by the study contract pharmacy and couriered to participants. Individuals who smoke ≥10 cigarettes per day and intend to quit within the next 30 days will be recruited through Public Health Units and Tobacco Control Area Networks throughout Ontario by word-of-mouth and the internet. Eligible participants will receive an email with a prescription for 12-week assigned medication and a letter to take to their physician. The recruitment and randomization will continue until 500 participants per arm have received medication. All participants will receive weekly motivational emails during the treatment phase. The primary outcome measure is the smoking status after 6 months, biochemically confirmed by mailed-in salivary cotinine. Follow-ups will be conducted through emails after 4, 8, 12, 26, and 52 weeks of starting the treatment to assess the smoking prevalence and continuous smoking abstinence. In addition, mailed-in saliva samples will be used for genetic and nicotine metabolism analyses. Furthermore, personality characteristics will be assessed using the Big Five Aspect Scales.

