#### Patient Visit to a Licensed Practitioner

All eligible participants will be required to visit their physician or another licensed prescriber within 5 weeks from the enrollment date to sign the prescription for their assigned medication. Reminder emails will be sent after 2 weeks of the enrollment date to make sure that the participants have booked an appointment to visit their practitioner. At the visit, participants will discuss their medical history, the medications they are on, and any other concerns they have regarding the treatment. At his or her discretion, a licensed practitioner may either sign the prescription for study medication or choose not to prescribe the assigned medication to their patient. The practitioner’s office will then fax the signed prescription to a mail-order pharmacy contracted to do the study that will then fill the prescription.

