#### Sample Size

In the 2 head-to-head RCTs of varenicline versus bupropion [6,7], participants were randomized 1:1:1 to varenicline, bupropion, or placebo arms with 341-345 participants in each group. In the trial conducted by Gonzales et al [6], the 9- to 52-week CARs were 21.9% in the varenicline group versus 16.1% in the bupropion group (OR 1.49, 95% CI 0.99-2.17, *P*=.057). In the trial conducted by Jorenby et al [7], the 9- to 52-week CARs were 23% in the varenicline group compared with 14.6% in the bupropion group (OR 1.77, 95% CI 1.19-2.63; *P*=.004). Because this is an effectiveness trial, we anticipate lower quit rates overall. Indeed, in our previous feasibility study [18], 7-day point prevalence abstinence (PPA) rates after 6 months (intention-to-treat analysis) were 18.9% in those who received varenicline and 17.4% in those who received bupropion.

To be sufficiently powered to detect a significant difference in the 26-week CARs, we plan to randomize 500 subjects to each medication arm. We predict that the real-world abstinence rates will be slightly lower than those observed in clinical trials and may be similar to what we found in our nonrandomized study that this protocol is based on [19]. Therefore, we assumed that the 26-week CAR in the varenicline-treated group would be 20% compared with 15% in the bupropion-treated group. At 500 subjects per group, we will have 80% power to detect a significant difference between groups at a .05 level of significance.

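### The set called intention-to-treat excludes randomised participants who did not receive their drug; receipt is an unblinded, post-randomisation event that can differ by arm

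*Protocol article*

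**What the plan says.** The Data Analysis section of the protocol article names the analysis intention-to-treat and defines its population as one "wherein all participants who are randomized to a treatment arm and receive their assigned medication are included in the final analysis". It gives the reason, cut here before its last word: "This method will be used to avoid any bias that can potentially arise because of crossover and dropouts, affecting the initial random assignment to treatment". The same section counts participants lost to follow-up, or without a saliva sample, as smokers.

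Several steps lie between randomisation and receipt. After Figure 2: "Those who are eligible will receive an email, including their medication assignment". The section on the visit to a practitioner then states: "All eligible participants will be required to visit their physician or another licensed prescriber within 5 weeks from the enrollment date to sign the prescription". It adds that, when seen, "a licensed practitioner may either sign the prescription for study medication or choose not to prescribe the assigned medication to their patient". The Blinding section says that pharmacists, primary care providers and research staff know the assignment.

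On numbers, the Abstract (Methods) says "The recruitment and randomization will continue until 500 participants per arm have received medication", whereas Sample Size says "we plan to randomize 500 subjects to each medication arm".

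**The concern.** An intention-to-treat set keeps everyone in the arm to which they were randomised. This one removes people by something that happens after randomisation and after the arm is known. A modified set of this kind can be harmless when the excluding event cannot depend on the assignment, for example under full blinding. Here it can: a participant may not pursue a drug they did not want, and a prescriber may refuse that particular drug.

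If one drug is pursued or prescribed less often, and those who drop out are less likely to quit, the remaining receivers in that arm are a more favourable group. Their quit rate then rises without any drug effect. The set underlies the main hypothesis, that varenicline is superior at 6 months. The article describes no analysis of all randomised participants.

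**Working it through.** **1. Order of events.** Eligibility screening → randomisation → arm disclosed by email → participant-arranged visit within 5 weeks → prescriber signs or declines → pharmacy dispenses → inclusion in the analysis set. Inclusion is decided at the last step, and every step after disclosure is unblinded.

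**2. The plan's own power figure.** Inputs from Sample Size: 500 per arm, 20% versus 15%, alpha 0.05, stated power 80%. Two-sided normal approximation: power = Φ[(d − 1.96·SE0)/SE1].
- SE0 = √(2 × 0.175 × 0.825/500) = 0.0240
- SE1 = √((0.20 × 0.80 + 0.15 × 0.85)/500) = 0.0240
- (0.05 − 1.96 × 0.02403)/0.02398 = 0.12, so power = 55%.

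The stated 80% is not reproduced (one-sided gives 67%). That is a separate matter. It is mentioned because 55% is the baseline in step 5.

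**3. Possible size of the selection bias.** Receipt rates and strata below are assumptions. In both scenarios the drugs are equally effective and the sample has two halves with different quit rates. The false-positive risk is for a two-sided 5% test with 500 receivers per arm.

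*Scenario A (strong selection).* Half quit at 25% and all of them receive drug; the other half quit at 8% and account for all non-receipt. The quit rate among receivers at overall receipt r is [0.5 × 0.25 + (r − 0.5) × 0.08]/r.
- r = 0.8: 0.149/0.8 = 18.6%
- r = 0.7: 0.141/0.7 = 20.1%
- r = 0.6: 0.133/0.6 = 22.2%

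*Scenario B (milder).* Half quit at 25%, half at 10%. Receipt is 80% everywhere except in the low-quitting half of one arm, where it is r_L. The quit rate among receivers in that arm is (0.4 × 0.25 + 0.5 × r_L × 0.10)/(0.4 + 0.5 × r_L).
- r_L = 0.8: 0.140/0.8 = 17.5% (no bias)
- r_L = 0.6: 0.130/0.7 = 18.6%
- r_L = 0.4: 0.120/0.6 = 20.0%

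| Scenario | Receipt by arm | Quit rate among receivers | Spurious difference | False-positive risk |
|---|---|---|---|---|
| B | 80% v 80% | 17.5% v 17.5% | 0 | 5% |
| B | 80% v 70% | 17.5% v 18.6% | 1.1 points | 7% |
| B | 80% v 60% | 17.5% v 20.0% | 2.5 points | 17% |
| A | 70% v 60% | 20.1% v 22.2% | 2.0 points | 12% |
| A | 80% v 60% | 18.6% v 22.2% | 3.5 points | 29% |

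**4. Does scoring non-receivers as smokers cure it?** Not fully. In scenario A, suppose non-receivers still quit at 8%. The true rate among all randomised is then 0.5 × 0.25 + 0.5 × 0.08 = 16.5% in both arms. Scoring non-receivers as smokers at 80% versus 60% receipt gives 14.9% versus 13.3%: a spurious 1.6 points with the sign reversed. This is smaller than 3.5 points but not zero.

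**5. Power for all randomised.** Assume 500 receivers per arm, equal receipt r, 20% versus 15% among receivers, and non-receivers quitting at q. N per arm = 500/r; the arm rates are 0.20r + (1 − r)q and 0.15r + (1 − r)q.

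| r | N per arm | q = 0 | q = 5% | q = 8% |
|---|---|---|---|---|
| 0.8 | 625 | 53% | 51% | 50% |
| 0.6 | 834 | 52% | 46% | 43% |

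**6. The two recruitment statements.** Randomising 500 per arm and having 500 per arm receive drug agree only if every randomised participant receives drug. If only 500 per arm were randomised and 60–80% received drug, there would be 300–400 receivers per arm, and power at 20% versus 15% would be 36–46%.

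**The case against.** The strongest reply is that nothing in the document shows receipt differing by arm. That is right: receipt can depend on the arm, and a reader might infer that it does, but no section says so. With equal receipt across arms and strata there is no bias.

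Second, the Inclusion and Exclusion Criteria remove many contraindications before randomisation and alike for both arms (for example seizure disorder, eating disorder, pregnancy, allergy to either drug and antidepressant use). This narrows the route through medical refusal. It leaves patient preference and prescriber discretion untouched.

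Third, a reader might infer that recruiting to 500 receivers per arm conceals unequal receipt. The document does not support that. Allocation is 1:1, so unequal receipt would show in the numbers randomised or dispensed by arm once these are reported. Figure 1, which is not shown here, gives the expected participant flow and may already contain the randomised number.

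Fourth, a reader might infer that analysing everyone is only a change of wording with a trivial loss of power. The loss is 2 to 4 points only if no non-receiver quits. The existing missing-outcome rule covers loss to follow-up and missing saliva, not non-receipt. Outcomes are timed from the start of treatment, which non-receivers do not have, and enrolment closed in January 2017, so their outcomes may not be recoverable.

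Finally, whether failing to obtain a prescription belongs to the outcome is a matter of interpretation. Study Aims refers to cessation rates with treatment, while the Objective speaks of real-world effectiveness of mailed drug. The wrong label and the unsupported claim of protection stand under either reading.

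**Conclusion.** The concern holds as a defect in the definition of the primary analysis set. The label is wrong, and the stated protection against bias does not follow, because inclusion depends on an unblinded event after randomisation that the arm can influence. This conclusion needs no figure.

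The size does. Without a readable receipt rate, the illustrations give about 1 to 3.5 points of spurious difference for receipt gaps of 10 to 20 points, or roughly 20% to 70% of the 5-point target, and zero under equal receipt. The upper end assumes that all non-receipt falls on people unlikely to quit. These figures show what is possible; they are not an estimate of bias in this trial. The conflict between the Abstract and Sample Size on what the 500 per arm counts is real and should be settled at the same time.

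**What to change.** - Make all randomised participants, by assigned arm, the primary analysis set.
- Relabel the receiver set modified intention-to-treat, report it as secondary, and remove the statement that it protects the random assignment.
- Report the numbers randomised and dispensed by arm.
- State how non-receivers are scored: for example as smokers, with time counted from randomisation or enrolment where outcome data exist. Add a sensitivity analysis over plausible non-receiver quit rates, allowed to differ by arm.
- Reconcile the Abstract (500 per arm having received medication) with Sample Size (500 per arm randomised).

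**Cost.** No new recruitment is needed. Absolute quit rates will be lower. With 500 receivers per arm and 60–80% receipt, power is about 43–53% for non-receiver quit rates of 0–8%, against 55% for receivers only. Where non-receivers were not followed, their outcomes rest on the scoring assumption, which is why the sensitivity analysis is needed.
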